#### 2.6.2. Effectiveness Outcomes

The primary effectiveness outcome is the CSS score at Week 6. The CSS is a scale for the subjective assessment of cough severity and frequency that is reported by the patient during the daytime (08:00–20:00) and nighttime (20:00–08:00), and each subdomain of the scale is assigned 6 points, from 0 to 5. The total score is calculated as the sum of the daytime and nighttime scores (0–10 points) [19]. The validity and replicability of the Korean version of CSS have been verified [20]. Until Week 9, participants will be instructed to self-evaluate the CSS twice a day and record the score in a cough diary. During the telephonic follow-up survey (Week 24), participants will be asked to respond on their cough symptoms during the daytime and nighttime of the previous day. For statistical analysis, the average value (total, daytime, and nighttime scores) of the CSS since the previous visit that has been recorded in the cough diary and will be collected at each visit (excluding the baseline visit) will be used, and the average value of the previous 7 days will be used for determining the status at the baseline visit. The investigator will educate the participants on how to write a cough diary at every visit and attempt to minimize omissions in records. If less than 70% of the cough diary distributed at each visit has been completed, the participant will be dropped out.

The secondary outcome measures include the CSS (at weeks 3, 9, and 24), cough visual analog scale (VAS), the Leicester Cough Questionnaire (LCQ), the Hull Airway Reflux Questionnaire (HARQ), Integrative Medicine Outcome Scale (IMOS), Integrative Medicine Patient Satisfaction Scale (IMPSS), a five-level version of the EuroQol Five-dimensional Descriptive System (EQ-5D-5L), the EuroQol visual analog scale (EQ-VAS), yin deficiency score, and serum biomarkers.

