All statistical analysis is based on a two-sided test, and the significance level is set at 0.05. For continuous data, the mean and confidence interval are presented, whereas for categorical data, the frequency and percentage are presented. Statistics on the demographic and socioeconomic characteristics are presented for each group. Depending on normality, continuous data are analyzed using the independent *t*-test or Wilcoxon rank sum test, whereas categorical data are analyzed using the chi-square or Fisher’s exact test. For analyzing the effectiveness outcomes, the mixed-effect model repeated-measures method will be used, with each group and visit as the fixed factor and the participants as the random factor. If necessary, variables that show statistical differences in demographics or variables that can affect chronic cough will be set as fixed factors and analyzed. Intragroup differences in values before and after treatment will be analyzed, based on normality, with the Student’s paired *t*-test or Wilcoxon signed rank test. The IMOS and IMPSS scores are analyzed using Fisher’s exact test. The repeated-measures analysis of variance method is used to compare the difference in trend change between groups for the effectiveness outcomes, and Dunnett’s procedure is used for correction of the multiple-comparison analysis. If necessary, subgroup analysis will be performed by categorizing the participants according to their baseline characteristics (chronic cough pattern identification [29], presence of yin deficiency [27], sex, age, etc.). For the analysis of safety outcomes, the chi-square or Fisher’s exact test will be performed to compare the number of adverse events in the study groups. In addition, AST, ALT, BUN, creatinine, and vital signs will be analyzed using a paired *t*-test or Wilcoxon signed rank test to determine differences from before to after treatment. No interim analysis has been planned. All statistical analyses will be performed by a statistician, independently of trial procedure, by using the statistical program SAS^®^ Version 9.4 (SAS Institute Inc., Cary, NC, USA). 

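### The mixed model stated for the effectiveness outcomes names no group-by-visit term and no Week 6 contrast, so as written it does not estimate the Week 6 CSS difference that is the primary effectiveness outcome

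*Protocol article*

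**What the plan says.** Section 2.6.2 (Effectiveness Outcomes) ties the primary effectiveness outcome to one time point: "The primary effectiveness outcome is the CSS score at Week 6". The same score at the other post-baseline visits is secondary: "The secondary outcome measures include the CSS (at weeks 3, 9, and 24".

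Section 2.8 (Statistical Analysis) then names a mixed-effect repeated-measures model for the effectiveness outcomes and lists its terms: "with each group and visit as the fixed factor and the participants as the random factor". The only further terms it allows, if necessary, are covariates: "variables that show statistical differences in demographics or variables that can affect chronic cough will be set as fixed factors and analyzed".

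Two other between-group analyses of continuous data appear in the same section:

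- "The repeated-measures analysis of variance method is used to compare the difference in trend change between groups for the effectiveness outcomes", with Dunnett's procedure for multiple comparisons.
- "Depending on normality, continuous data are analyzed using the independent *t*-test or Wilcoxon rank sum test", a general sentence that follows the one on demographic and socioeconomic characteristics and names no outcome and no visit.

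Section 2.8 does not say which visits enter the mixed model, or whether the baseline value is a response or a covariate.

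**The concern.** A model with group and visit main effects and a participant random effect has a single group coefficient, assumed equal at every visit. That coefficient answers how the groups differ on average over the modelled visits. The primary outcome asks how they differ at Week 6.

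This design gives little reason to expect the two to agree. Drug is taken for six weeks (sections 2.1 and 2.5), so Weeks 9 and 24 are off drug. Diary CSS is averaged since the previous visit (section 2.6.2), so the Week 3 value includes the first days of treatment. The Week 24 value is a telephone report on the previous day only. If baseline is a response, a visit is added at which randomisation makes the expected difference zero.

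At stake is whether the result reported for the primary effectiveness outcome is in fact the Week 6 treatment effect.

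**Working it through.** **1. The plan's own figure.** Section 2.7 needs 24 participants and allows 20% dropout: 24 / (1 − 0.20) = 30, or 15 per group. This reproduces. The point does not affect the sample size; n = 15 per group is used below.

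**2. What the group coefficient estimates.** With complete data and a participant random intercept, the group coefficient of a group + visit model is the simple mean of the k visit-specific differences. Each visit has weight 1/k: Week 6 counts 1/5 if baseline is a response and 1/4 with Weeks 3, 6, 9 and 24 only. With missing data the coefficient is a weighted average instead.

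**3. Size under assumed patterns.** The article gives no expected differences, so these are assumptions. Let the Week 6 effect be δ and the effect at baseline and Week 24 be nil.

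| Effect at Weeks 3, 6, 9, 24 | Baseline a response (k = 5) | Post-baseline only (k = 4) |
|---|---|---|
| 0.5δ, δ, 0.5δ, 0 | 2.0δ/5 = 0.40δ | 2.0δ/4 = 0.50δ |
| δ, δ, δ, 0 | 3.0δ/5 = 0.60δ | 3.0δ/4 = 0.75δ |
| δ, δ, δ, δ (constant after baseline) | 4.0δ/5 = 0.80δ | 4.0δ/4 = 1.00δ |

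If only Weeks 3 and 6 were modelled, with half the effect at Week 3, the result would be (0.5δ + δ)/2 = 0.75δ.

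A generalised least squares calculation with assumed CSS differences of −0.5, −1.0, −0.6 and −0.2 at Weeks 3, 6, 9 and 24 agrees. The group + visit model gives −2.3/5 = −0.46 with baseline as a response and −2.3/4 = −0.575 without it. Adding group-by-visit and taking the Week 6 contrast gives −1.00 in both cases.

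**4. Precision and power.** Take a Week 6 difference of 1 SD, n = 15 per group, two-sided 0.05 and common correlation ρ between visits (assumed).

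- Pooled coefficient: SE = SD × √[(1 + (k − 1)ρ)/k × 2/n].
- Week 6 contrast: SE = SD × √(2/n) = SD × √(2/15) = 0.365 SD; power 75%.
- At ρ = 0.6, k = 4: SE = SD × √(0.70 × 2/15) = 0.306 SD; power 35% for 0.50δ and 66% for 0.75δ.
- At ρ = 0.6, k = 5: SE = SD × √(0.68 × 2/15) = 0.301 SD; power 25% for 0.40δ and 49% for 0.60δ.
- At ρ = 0.3, k = 4: SE = SD × √(0.475 × 2/15) = 0.252 SD; power 82% for 0.75δ, above the 75% of the Week 6 contrast. For this pattern the two cross at ρ of about 0.42.

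The direction of the power difference therefore depends on ρ and on the pattern. The difference in what is estimated does not depend on ρ.

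**5. Whether another analysis in section 2.8 fills the gap.** The repeated-measures ANOVA, as described, "is used to compare the difference in trend change between groups for the effectiveness outcomes". That is a global test over visits and yields no Week 6 estimate or interval. The t-test or Wilcoxon sentence is not tied to Week 6 CSS. The paired tests are within group. Dunnett's procedure compares several levels with one control; with two arms it does not provide a between-group comparison at Week 6.

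**The case against.** The strongest reply is that silence is being read as exclusion. The article lists factors in one condensed sentence and nowhere says main effects only. A mixed model for repeated measures is commonly fitted with group-by-visit and read at a named visit, and an analysis plan that is not shown may say so. A reader might infer that the Week 6 difference can never come out of this plan. The article does not support that: the interaction is unnamed rather than ruled out, and the general two-sample test could be applied at Week 6. What remains is that the article does state its fixed and random factors, and as stated they do not target its own primary time point. That is a specification to correct, not merely a detail left for later.

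Three further inferences also go too far:

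- **A certain loss of power.** The pooled test can be the more powerful one, even with no effect at Week 24, as step 4 of the working shows.
- **A halved effect for outcomes measured twice** (yin deficiency score, serum biomarkers). This holds only if the pre-treatment value is a response. If it is not, Week 6 is the only response and the full effect is returned.
- **A confirmatory trial sized on the wrong effect.** Nothing in the article says a later trial will be sized on this estimate. The feasibility measure that section 2.6.1 expressly links to planning that trial is the recruitment period.

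The set of modelled visits is also unstated, so inclusion of the off-drug visits is possible but not certain.

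**Conclusion.** The point holds in a limited form. The model in section 2.8, fitted as written, estimates an average of visit-specific differences and not the Week 6 CSS difference that section 2.6.2 makes primary. Nothing else in section 2.8 is tied to that difference.

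The size is conditional. With nil effect at Week 24 and half to full effect at Weeks 3 and 9, the coefficient is 0.50 to 0.75 of the Week 6 effect on four post-baseline visits, and 0.40 to 0.60 with baseline as a response. These ranges rest on the assumed patterns, complete data and a participant random intercept. If the effect were the same at every modelled visit, the two estimates would coincide. No general claim about power follows.

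Severity is moderate. Section 2.6.1 makes feasibility the primary purpose, efficacy is preliminary, and section 2.7 sets the sample size by a rule of thumb without a power target.

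**What to change.** In section 2.8, or in the statistical analysis plan:

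- add the group-by-visit interaction to the mixed model;
- state that the primary effectiveness result is the between-group contrast in CSS at Week 6, with its 95% CI;
- report the CSS at Weeks 3, 9 and 24 as secondary contrasts from the same model;
- state whether baseline enters as a response or as a covariate.

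The cost is a sentence or two; no data are added and the sample size is unchanged. The downside is some precision: under the assumptions in the working, the Week 6 contrast has SE 0.365 SD, against 0.306 SD (ρ = 0.6) or 0.252 SD (ρ = 0.3) for the pooled estimate on four visits. The gain is that the reported estimate is the stated endpoint.

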### 2.4. Randomization and Blinding

The randomization sequence will be generated by block randomization method (mixing block sizes of two and four) without stratification. The allocation ratio for each group is 1:1. The randomization sequence will be generated using the statistical program SAS^®^ Version 9.4 (SAS Institute Inc., Cary, NC, USA) by a medical statistician, independent of the interventions and evaluations in this clinical trial. Participants who meet all the eligibility criteria will be allocated from the minimum available number to each group. 

In this clinical trial, all participants, investigators, and outcome assessors are blinded. Each participant’s group information according to the randomization order will be put in an opaque sealed envelope. It will not be disclosed until the end of the clinical trial, except when it is unavoidable to view group information due to the occurrence of a serious adverse event.

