### 2.7. Sample-Size Calculation

This is the first exploratory clinical trial to evaluate the feasibility and preliminary effect of *Maekmundong-tang* administration in patients with nonspecific chronic cough. Therefore, there are no prior literature references for sample size calculation. Referring to a study that recommended a minimum of 12 people per group in a preliminary study in the field of life sciences [28], a total of 24 participants, with 12 participants per group, are needed. Considering a dropout rate of 20%, a total of 30 participants, 15 in each group, were specified as the target sample size.

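### Section 2.8 lets baseline significance tests, or undefined need, decide which covariates enter the effectiveness model, and does not say whether the adjusted model is the main one

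*Protocol article*

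**What the plan says.** For the effectiveness outcomes, section 2.8 specifies that "the mixed-effect model repeated-measures method will be used, with each group and visit as the fixed factor and the participants as the random factor". The next sentence opens with a condition, "If necessary, variables that show statistical differences in demographics", and continues to a second route into the model. In full, the operative words are "variables that show statistical differences in demographics or variables that can affect chronic cough will be set as fixed factors and analyzed".

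So there are two ways in: a statistical difference in demographics, or a capacity to affect chronic cough. Both depend on a need that is not defined. No covariate is named, not even baseline CSS, which section 2.6.2 derives from the seven days before the baseline visit. The section does not say whether the model with added factors replaces the group-and-visit model or stands beside it.

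The general testing rule is "All statistical analysis is based on a two-sided test, and the significance level is set at 0.05". Allocation, under section 2.4, uses a "block randomization method (mixing block sizes of two and four) without stratification". The primary effectiveness outcome is CSS at Week 6 (section 2.6.2), and section 2.6.1 gives feasibility as the primary purpose.

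**The concern.** In a properly randomised trial, baseline differences between arms arise by chance. A baseline test therefore does not show whether a variable predicts the outcome, which is the only good reason to adjust for it. A rule based on that test adds irrelevant variables at the significance level and mostly passes over useful ones.

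The second route has a different weakness. With no list, number or timing, it allows the covariates to be settled once results are visible.

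At stake are the precision of the Week 6 comparison and whether the nominal 5% level and the confidence interval describe what was done. Section 4 expects the results to inform clinical practice and insurance coverage, so the effectiveness estimate will be read as more than a by-product of the feasibility work.

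**Working it through.** **Inputs from the article**
- Two-sided 0.05 (section 2.8).
- Evaluable number: "a total of 24 participants, with 12 participants per group, are needed" (section 2.7).
- Target: "Considering a dropout rate of 20%, a total of 30 participants, 15 in each group, were specified as the target sample size" (section 2.7).

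**The plan's own figure.** 24 / (1 - 0.20) = 30, or 15 per group. This reproduces. The article gives no power, effect size or error rate for the covariate rule.

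**Assumptions, not in the article.** A single-endpoint ANCOVA stands in for the Week 6 contrast of the mixed model. Covariates are independent and normal. The baseline test is taken at the general 0.05 level. Power is for a true difference of 1 SD of the outcome.

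**Step 1: how often the baseline test fires.** With k independent variables, the chance that at least one qualifies is 1 - 0.95^k: 5% for k = 1, 18.5% for k = 4 and 26.5% for k = 6. Simulation at 15 per arm gave 17.5-20% for k = 4 and about 27% for k = 6.

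**Step 2: the baseline test applied mechanically.** One covariate, 15 per arm, 200,000 runs per setting:

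| Correlation with outcome | Type I error, rule | Power, unadjusted | Power, rule | Power, prespecified |
|---|---|---|---|---|
| 0 | 5.05% | 75.4% | 74.9% | 73.7% |
| 0.3 | 4.81% | 75.3% | 75.3% | 77.7% |
| 0.5 | 4.39% | 75.1% | 75.7% | 84.9% |
| 0.7 | 3.67% | 75.3% | 76.9% | 95.2% |

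At 12 per arm and correlation 0.5, the three powers are 64.8%, 65.2% and 75.0%. With 2 to 6 covariates, type I error under the rule stayed at about 3-5%.

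The reason is simple. With one covariate the test fires in 5% of trials, so the other 95% are analysed unadjusted. A covariate with correlation 0.5 would remove 0.5^2 = 25% of the outcome variance, but the rule takes that gain in only one trial in twenty. Type I error drifts below 5% because the trials with the largest chance imbalance are the ones that get adjusted.

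**Step 3: free choice after seeing results.** Here the smallest p-value over all covariate subsets is reported, at 15 per arm. R2 is the share of outcome variance explained jointly by the k candidates. There were 200,000 runs for k = 1 and 2,000-4,000 otherwise, so simulation error is about 0.3-1 point for k above 1.

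| Candidates k | R2 = 0 | R2 = 25% | R2 = 50% |
|---|---|---|---|
| 1 | 5.8% | 7.3% | about 8.5% |
| 2 | 7.3% | 8.9% | 11.7% |
| 4 | 8.4% | 12.4% | 16.7% |
| 6 | 11.2% | 16.5% | 23.3% |

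Results at 12 per arm are similar (k = 6: 11.9%, 18.0%, 21.9%).

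**Step 4: covariates fixed in advance.** Type I error is 5.0-5.1% with one covariate. With up to six it is about 3.6-5.7%, the scatter being simulation error.

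**The case against.** The best defence has four parts.

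First, this is a feasibility trial with a rule-of-thumb sample size and no power target, and no decision rule in the article turns on the effectiveness p-value. That stands, and it limits severity.

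Second, a separate analysis plan may list covariates before unblinding. That could close the second route. It would not rescue the first, because the article states baseline significance as a criterion and a plan that followed it would inherit the fault.

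Third, a reader might infer that important imbalances must go unadjusted, since significance at 15 per arm needs a difference of t(0.975, 28) x sqrt(2/15) = about 0.75 SD. The text does not support that. The second route carries no significance condition, so a prognostic variable can enter at any imbalance, and the first route covers demographics only.

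Fourth, the power loss is measured against prespecified adjustment. Against the stated group-and-visit model the rule costs essentially nothing (75.7% v 75.1% at correlation 0.5). That is correct and is how the figures should be read.

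Two further inferences go too far. A reader might conclude that the added factors replace the main model; the section leaves this open, and a supplementary adjusted analysis is a possible reading. A reader might also take "Statistics on the demographic and socioeconomic characteristics are presented for each group" as a plan for baseline testing, but that sentence is purely descriptive.

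**Conclusion.** The point holds at modest severity, as two separate faults and an ambiguity.

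1. **Baseline significance as a criterion.** It is unsound but does not raise the false-positive rate. Its cost is forgone precision: about 9 points of power at correlation 0.5 (84.9 - 75.7 = 9.2) and 18 at 0.7 (95.2 - 76.9 = 18.3), but only 2 at 0.3 and none for an unrelated covariate. These figures assume a 1 SD effect, 15 per arm and one covariate.
2. **Open wording.** It permits result-driven choice. The range of about 6-23% applies only if the most favourable model is reported from 1 to 6 candidates. The article gives neither the number of candidates nor their prognostic strength, so no single inflated error rate can be attributed to the plan. Nor does it say that covariates will be chosen after results are seen; it fails to exclude it.
3. **Main model.** The section does not identify it.

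All simulated figures come from an ANCOVA approximation and not from the full repeated-measures model.

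**What to change.** Reword section 2.8, or settle it in the analysis plan before unblinding:
- Delete statistical difference at baseline as a reason to add a covariate.
- Fix a short covariate list for the main model on prognostic grounds, whatever imbalance is observed: baseline CSS, which is already collected, plus at most one or two others. If baseline CSS is modelled as a response visit, do not also enter it as a covariate.
- State that this is the main model for CSS at Week 6.
- Label every other adjusted model as a sensitivity analysis that cannot replace it.

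The cost is wording and an early decision on covariates. No participant, visit or measurement is added. What is lost is the freedom to add covariates to the main model later, and a degree of freedom for each listed covariate: with an unrelated covariate, power at 15 per arm fell from 75.4% to 73.7%. That is why the list should be short.

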(18) those with average daytime cough symptom score (CSS) < 2 points and night-time CSS < 1 point according to the cough diary recorded for the 7 days immediately before the baseline visit

(19) those who are judged to be inappropriate for participating in this study by the investigators

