The investigator will provide a multidimensional behavioral therapy (speech pathology therapy) guideline, which is a non-pharmacological treatment for cough, to all participants and educate the participants about this therapy [15]. This includes the creation of awareness that repetitive coughing is not beneficial and that coughing can be controlled by oneself through the suppression of the cough reflex that is induced by stimuli by swallowing saliva or water, or breathing with pursed lips when about to cough [15]. In addition, the education includes the vocal hygiene method, which ensures the supply of moisture to reduce laryngeal irritation, and psychological education counseling therapy, which helps patients recognize that chronic cough is difficult to treat and thereby set realistic treatment goals [15].

During the clinical trial period, new intake of any prescription drugs and over-the-counter medicines, except for investigational products and drugs allowed at screening visit, should be avoided. In particular, the trial should be discontinued if the following medications or treatments are required due to the participants’ circumstances or clinical condition: ACE inhibitor, DPP-4 inhibitor, antitussive, expectorants, steroid, antileukotrienes, anticholinergic, LABA, oral antihistamines, traditional Korean treatment (e.g., herbal medicine, acupuncture, etc.) to improve chronic cough, and other drugs or treatments that, in the investigator’s judgment, may affect the results of the clinical trial. 

At any time during the trial, the participants can voluntarily withdraw their participation for reasons such as dissatisfaction with the treatment effect. If participants are no longer able to participate in the trial due to adverse events or intercurrent diseases during the trial or have received the contraindicated drugs, which may affect the research outcomes, the participants will be dropped from the study at the investigators’ discretion. 

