Herbal medicine is characterized by a multicomponent, multitarget formulation [33]. Therefore, it is promising for treating chronic cough with unknown or intractable causes. *Maekmundong-tang* is frequently used for the empirical treatment of nonspecific chronic cough in the East Asian traditional medicine clinical setting. Although the effects of *Maekmundong-tang* on cough related to chronic airway diseases and cough hypersensitivity accompanied by chronic cough have been reported through various experimental and clinical studies [10,11,12,13], robust evidence is still lacking. In addition, although a clinical trial comparing the effect of *Maekmundong-tang* with a placebo control group in patients with chronic dry cough was conducted in the Republic of Korea [34], it did not rule out common causes of chronic cough such as the upper airway cough syndrome. Furthermore, the effect of *Maekmundong-tang* on chronic cough has not been reported since the time nonspecific chronic cough was clearly defined in a recent clinical practice guideline [6]. Therefore, in this exploratory clinical trial of *Maekmundong-tang* in patients with nonspecific chronic cough, the feasibility of large-scale clinical trials, such as the recruitment, adherence, and completion rates, will be confirmed. In addition, the existing health insurance-covered herbal medicine was used in the control group to explore the possibility of medical insurance benefits for *Maekmundong-tang* through cost-effectiveness analysis. 

For the control group intervention, *Saengmaek-san*, for which cough is an indication, and which has been actively studied for chronic cough patients through clinical studies [35,36,37], has been specified. In particular, as nonspecific chronic cough is mainly characterized by dry cough [6,35], *Saengmaek-san*, which has been used for dry cough because of its pulmonary mucolytic effect to suppress cough [38], has been specified as the control intervention based on consultation with experts in respiratory medicine. Through this, we plan to not only explore the preliminary effects, safety, and cost-effectiveness of *Maekmundong-tang* but also observe the clinical effects before and after administration of *Maekmundong-tang* and *Saengmaek-san* for nonspecific chronic cough.

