## 4. Conclusions

In conclusion, we will explore the feasibility of future large-scale clinical trials and provide clinical evidence that can be immediately applied to the clinical setting by exploring the symptom improvement effect of *Maekmundong-tang* in patients with nonspecific chronic cough. In addition, the results of this study are expected to provide scientific evidence for the expansion of the health insurance coverage for chronic cough by comparing the cost-effectiveness of *Maekmundong-tang* with that of *Saengmaek-san*, which is an insurance-covered herbal medicine for cough. 

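### Within-arm before-after tests cannot show a drug effect on cough here, and the test named for laboratory values and vital signs does not compare the arms

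*Protocol article*

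**What the plan says.** **Planned tests (Protocol article, section 2.8).** Effectiveness outcomes go to a mixed model with group and visit as fixed factors, and a repeated-measures ANOVA compares trends between groups. Within-arm testing is then added: "Intragroup differences in values before and after treatment will be analyzed, based on normality, with the" paired t-test or its signed-rank counterpart. The general rule is: "All statistical analysis is based on a two-sided test, and the significance level is set at 0.05".

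**Use of before-after change (section 3, Discussion).** Besides exploring the preliminary effects of *Maekmundong-tang*, the trial will "observe the clinical effects before and after administration of" both medicines.

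**What both arms share.** The control is active. Under section 2.5 the investigator gives a behavioural cough therapy guideline "to all participants and educate the participants about this therapy". Table 1 schedules this education at Visits 2 to 5 (Weeks 0 to 9).

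**Entry and baseline.** Criterion 18 (section 2.3) excludes people with low average daytime and night-time CSS "according to the cough diary recorded for the 7 days immediately before the baseline visit". Section 2.6.2 takes the baseline CSS from the previous 7 days, which is the same window.

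**Safety (section 2.8).** Adverse events are compared between groups. For the rest, "AST, ALT, BUN, creatinine, and vital signs will be analyzed using a paired" t-test or signed rank test of change from before to after treatment.

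**Claim (section 4).** The trial is to "provide clinical evidence that can be immediately applied to the clinical setting".

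**The concern.** Randomisation protects the contrast between arms. It does not protect the change within an arm, which adds together any drug effect, the behavioural therapy, regression to the mean, natural course and expectation. With an active control and no untreated group, nothing in the design separates these. Two significant paired p-values could be reported as two medicines that work when neither has done anything.

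The risk is practical. A comparison with 12 to 15 people per arm is imprecise, so significant paired tests may become the result that is quoted.

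The safety point is distinct. A paired test on ALT within each arm asks whether the mean moved. It does not ask whether it moved more under one medicine than under the other, which is the question a randomised comparison can answer.

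**Working it through.** **1. The plan's own figure.** Section 2.7 says "a total of 24 participants, with 12 participants per group, are needed" and allows 20% dropout: 24 / (1 − 0.20) = 30, or 15 per arm. This reproduces. The 12 per group is a cited rule of thumb, so there is no power calculation to check.

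**2. Paired test when the change is not due to the drug.** Let d be a common non-drug change in SDs of the change score. The two-sided 5% paired t-test rejects with the probability given by a non-central t with n − 1 degrees of freedom and non-centrality d√n. For example, d = 0.5 and n = 15 gives 0.5 × √15 = 1.94.

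| d | n = 12 | n = 15 |
|---|---|---|
| 0 | 5% | 5% |
| 0.25 | 12% | 15% |
| 0.5 | 35% | 44% |
| 0.8 | 71% | 82% |
| 1.0 | 88% | 95% |

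At d = 0.5 and n = 15, the chance that at least one of two identical arms is significant is 1 − (1 − 0.438)² = 68%.

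**3. Simulation with the CSS entry rule.** The article gives no CSS standard deviation, reliability or expected non-drug change, so these are assumptions:
- daytime mean 2.2 (SD 1.0) and night-time mean 1.2 (SD 0.9), with day-night correlation 0.5;
- reliability of the averaged score 0.5, 0.7 or 0.85, the same at baseline and follow-up;
- a common non-drug fall of 0, 0.5 or 1.0 points on the 0 to 10 total;
- two identical arms of 15, entry applied to the baseline window, 2,000 runs per scenario.

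Criterion 18 was run in two ways: literally (excluded only if daytime is below 2 *and* night-time is below 1), and as if each threshold had to be met.

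Percentage of within-arm paired tests with p < 0.05 and no drug effect (range over reliability):

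| Common non-drug fall | Literal *and* | Each threshold |
|---|---|---|
| 0 (regression to the mean only) | 6 to 13% | 15 to 40% |
| 0.5 points | 48 to 66% | 80 to 84% |
| 1.0 points | 87 to 99% | 98 to over 99% |

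The between-arm t-test on change rejected in 4.0 to 5.8% of runs across all scenarios, including those at 12 per arm. With no selection and no common fall, the within-arm test was at its nominal level (4.7% at reliability 0.7).

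Under the literal rule, regression to the mean moved the CSS by only 0.09 to 0.32 points. Most of the inflation comes from the shared non-drug fall.

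**4. Precision of the between-arm comparison.** In SDs of the outcome, the unadjusted 95% CI half-width is t(0.975, 28) × √(2/15) = 0.75 at 15 per arm and t(0.975, 22) × √(2/12) = 0.85 at 12. Baseline adjustment multiplies this by about √(1 − r²). For an assumed r of 0.6 to 0.8 the factor is 0.8 to 0.6, giving 0.60 to 0.45 SD at 15 per arm and 0.68 to 0.51 SD at 12.

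**5. Safety text side by side.** In section 2.8, the adverse-event sentence compares the study groups. The next sentence, on laboratory values and vital signs, names only paired tests. Liver and kidney tests are taken at screening and Week 6 (section 2.6.3), so the data for a between-arm comparison are already collected.

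**The case against.** The strongest reply is that inference on effectiveness is already between arms: the mixed model and repeated-measures ANOVA are the main analyses, and the paired tests take one supplementary sentence. That stands. A reader might infer that the paired tests carry the trial's conclusion on efficacy, and the article does not say so. A reader might also infer that the clinical-evidence claim in section 4 rests on them. Section 4 never mentions them, and section 2.7 calls the trial exploratory and its effect preliminary.

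On safety, section 2.8 also has a general sentence assigning continuous data to an independent t-test or rank sum test. It follows the sentence on demographics, and the safety text then names its own tests, but it could be read to cover laboratory values. It would therefore be too strong to say that no between-arm laboratory test is planned. Nor do the cough mechanisms extend to these measures: there is no reason to expect behavioural therapy or CSS entry to move AST or creatinine.

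On size, truncating the baseline at its mean and assuming a 0.3 to 0.5 SD non-drug improvement would give rates of about 75 to 97% at 15 per arm. Criterion 18 is not such a rule, and the article supports no particular improvement.

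What the reply does not remove is the Discussion sentence that treats before-after change as the medicines' clinical effects.

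**Conclusion.** The concern holds as a matter of interpretation and reporting. A significant within-arm fall in cough scores cannot be attributed to either medicine in this design. That conclusion needs no numerical assumption, because it follows from the active control, the shared therapy and the common window for entry and baseline. The size does need assumptions. At 15 per arm with no drug effect, the illustration gives 6 to 13% from regression to the mean alone under the literal criterion 18. With a common 0.5-point fall it gives roughly 50 to 85% across both readings of that criterion, against about 5% for the between-arm test.

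The safety limb is separate and narrower: the test named for laboratory values and vital signs does not compare the arms, and the text should say plainly that they will be compared.

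The main effectiveness model and the feasibility aims are unaffected. The correction is worth making before analysis but does not put the trial's primary purpose in doubt.

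**What to change.** - **Section 2.8, effectiveness:** drop the intragroup significance tests. Report within-arm change descriptively with confidence intervals, and base every effect statement on the between-arm difference adjusted for baseline, with its 95% CI.
- **Section 2.8, safety:** for AST, ALT, BUN, creatinine and vital signs, estimate the between-arm difference at Week 6 adjusted for the pre-treatment value, with 95% CI.
- **Section 3:** do not call before-after change within an arm a clinical effect of the medicine.
- **Section 4:** describe the result as feasibility findings plus a preliminary between-arm estimate, not as evidence for immediate clinical use.

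**Cost:** wording and a few lines of analysis code, with no new data, visits or participants. The stated claims become less favourable, and the between-arm laboratory comparison will be imprecise with 12 to 15 per arm.
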